# **Introduction and background**

**Physiologic and predisposing factors in the development of acute and chronic pain**

The experience and development of pain may be influenced by a number of physiological, psychological and psychosocial factors. However, our knowledge of the mechanisms responsible for acute and chronic pain is still incomplete. We now little of the physiological mechanisms responsible for acute and chronic pain, thus it is yet unknown whether individuals with a particular sensitive pain perception exists, and if this ability is hereditary. Hereditary pain sensitivity may increase the risk of developing acute and chronic pain pathology.

It has been hypothesized that the predisposition for developing central sensitization in response to injury is hereditary, and may explain differences in susceptibility to developing severe acute, and chronic pain(1). Thus, central neuronal sensitization is presumed to play an important role in a number of different pain conditions, such as osteoarthritis, fibromyalgia and post-operative pain (1).

In order to investigate the basic physiological mechanisms of pain, our research group has worked extensively with experimental physiological pain models (2-4). In an analysis of previous studies we have demonstrated that healthy individuals exposed to identical pain stimuli demonstrate very different degrees of secondary hyperalgesia areas. Concomitantly, results from these studies suggest, that secondary hyperalgesia areas may be a physiological phenomenon that can be identified. Further, that areas of secondary hyperalgesia may predict pain responses of the single individual (4).

In a preliminary study we further investigated subjects with large and small areas of secondary hyperalgesia, by applying imaging techniques ((f)MRI), and demonstrated anatomical and functional cerebral differences between these phenotypes (5). Finally, our investigations suggest that pain sensitivity and psychological vulnerability may be associated(5).

Results from other studies indicate that pain sensitivity may be hereditary with a 50% genetic contribution to the pain variation. Moreover, that pain sensitivity evaluated preoperatively, may predict the magnitude of the postoperative pain. This confirms that pain sensitivity may be influenced by individual factors. (6-8)

**Hyperalgesia models and phenotyping of study participants**

A standardised burn injury in the skin provokes reversible primary and secondary hyperalgesia in healthy volunteers. Injury-induced primary hyperalgesia is located in the traumatised area and is characterised by reduced thresholds for thermal and mechanical stimulation. Secondary hyperalgesia is located around the traumatised area, and is characterised by reduced thresholds for mechanical stimulation only (9, 10).

Previous studies have demonstrated that secondary hyperalgesia is a result of central changes in part due to sensitization in response to nerve signals transmitted in non-nociceptive Aβ-nervefibers (1, 9). Thus, this method can be used in investigation of the basic physiologic pain response.

Secondary hyperalgesia can be provoked by a number of different conditioning stimuli, and according to previous studies this is a robust phenomenon (10-12). Hence, this method can be used to investigate basic pain physiology, and applied when investigating different pharmaceutical interventions in reducing secondary hyperalgesia.

Previous studies have investigated secondary hyperalgesia with multiple stimulation modalities, and possible carry-over effect cannot be ruled out. Studies investigating the reproducibility of the area of secondary hyperalgesia are therefore needed.

**Association between pain sensitivity and psychological vulnerability**

Finally, our studies indicate that an association between psychological vulnerability and secondary hyperalgesia areas may exist (5). Several clinical studies have demonstrated an association between psychological variables and the experience of pain (13-15). To evaluate psychological vulnerability, the two psychological tests, the Pain Catastrophizing Scale (PCS) (16) and the Hospital Anxiety and Depression Score (HADS) supplement each other (17). HADS is a 14 point questionnaire that aims to identify symptoms of depression and anxiety, and is applicable in both a hospitalised and non-hospitalised population (18). PCS is a 13 point questionnaire designed to identify the three central elements in catastrophizing: Rumination, magnification, and helplessness, and is also applicable in both the hospitalised and non-hospitalised population (19).

With this prospective study we aim to investigate if pain sensitivity, evaluated by areas of secondary hyperalgesia following a standardised heat injury, is a physiological and reproducible phenomenon that characterizes the single individual. Furthermore we aim to investigate the association between the areas of secondary hyperalgesia and the individual psychological characteristics evaluated by PCS and HADS in healthy male volunteers.

# **Aim**

The aim with this prospective, observational and descriptive study is to validate previous results from retrospective investigations that indicate that secondary hyperalgesia is a robust and reproducible phenomenon, with a low intra-individual and a high inter-individual variability. Moreover, we aim to validate that the degree of secondary hyperalgesia can be applied as a phenotypic phenomenon and a biomarker for the excitability of the central nervous system. Lastly we aim to investigate if the area of secondary hyperalgesia can be associated with the individual psychological vulnerability in the study participants.

In a prospective cohort of 50 healthy volunteers we aim to:

1. Investigate the size of the area of secondary hyperalgesia following brief thermal sensitization on four different study days.
2. Investigate heat pain detection thresholds and pain during 1 min. thermal stimulation of the skin.
3. Determine the psychological vulnerability evaluated by the Hospital Anxiety and Depression Scale and the Pain Catastrophizing Scale.

# **Outcomes**

**Primary outcome**

To determine the intra- and inter-individual variance, and the inter- and intra-observer variance of the secondary hyperalgesia areas following brief thermal sensitization on 4 separate experimental days with two different observers.

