# **METHODOLOGY**

## **General procedure**

On the study days all study participants will be tested lying in the supine position. The study will be conducted in a quiet secluded room, where only the study participant and the investigator will be present.

The study participants will be tested with 3 types of pain conditioning on four separate study days. The 3 types of pain conditioning consist of Brief Thermal Sensitisation (BTS), Heat Pain Detection

Threshold (HPDT), and Long Thermal Stimulation (LTS), (see Clinical evaluations). HPDT and LTS are conducted subsequent to BTS. , the order of the stimulations (HPDT and LTS) is randomised for each patient and each experimental day, by a randomisation schedule developed by Copenhagen Trial Unit. Likewise, the investigators/observers responsible for testing and data registration will also be randomised, so the same investigator will not be responsible for 2 consecutive experimental days. There will be 2 different investigators responsible for the testing. The randomisation schedule is stored in sealed and opaque envelopes to secure adequate allocation concealment

The study participants will be tested with three types of pain conditioning on four separate experimental days. Furthermore, the study participants will complete the two psychological tests, PCS and HADS (see Assessments and tests)

The study participants will be tested with the following types of pain conditioning:

1. Brief Thermal Sensitisation (BTS). The test is conducted centrally on the anterior part of the right thigh. BTS will be conducted at the time: 0 min. (see Assessments and tests).
2. Heat pain detection threshold (HPDT). The test is conducted centrally on the anterior part of the dominant lower arm. HPDT (see Assessments and tests) will be conducted at the time: 7 or 10 min. depending on the randomisation (see Randomisation).
3. Long thermal stimulation (LTS). The test is conducted centrally on the anterior part of the non-dominant lower arm. A continuous VAS-measurement will be performed during the test. The test will be conducted at the time: 7 or 10 min. depending on the randomisation (see Randomisation).

The entire study consists of one screening day and four identical study days. The screening and study days will proceed as follows:

Screening day:

- Oral information regarding the project is delivered by the primary investigator. The participant will be given time to consider the information.

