- Short medical history by the primary investigator. Thorough screening of in- and exclusion criteria. Measurement of height, weight, blood pressure and pulse.
- In order to familiarise the study participant with the types of pain conditioning, the 3 types of pain conditioning test are presented and performed on the study participant.
- Distribution of PCS and HADS (in Danish), together with an opaque envelope, in which the answered test are to be put, and a sealed envelope will be returned to the primary investigator on the first study day.
- Potentially clarifying questions concerning the study or PCS and HADS are answered.

Study day 1, 2, 3, and 4:

- Inspection of signed informed consent and written authority.
- Returning of the filled in PCS and HADS questionnaires in a sealed opaque envelope to ensure that the investigators cannot access the data prematurely (study day 1). The envelope is opened when the study participant have completed the four experimental days.
- The study participant is placed on a bed in a supine position.
- Commencement of study:
  - 0 min: Brief thermal sensitisation.
  - 7 min: HPDT or LTS (depending on the randomisation)
  - 10 min: HPDT or LTS (depending on the randomisation)

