**Assessment of secondary hyperalgesia**

The area of secondary hyperalgesia is quantified after stimulation with a 19G monofilament (von Frey hair) in 4 linear paths arranged in 90° around the centre of stimulation. Stimulation will begin 15 cm. from the centre of stimulation and advance in steps of 5 mm. with 1 second intervals towards the centre of stimulation. When the participant states a clear change in sensation the place will be marked with a felt pen and the transverse and longitudinal axes will be measured for later area calculation.

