## **Plan of statistical analysis**

To determine the variance of the areas of secondary hyperalgesia derived respectively from the study participant, the experimental day and the observer, a variance component model will be employed, to investigate which of these three types of variance is the most influential of the total variance.

’Limits of agreements’ plot for agreement between areas of secondary hyperalgesia on different experimental days and different observers will be developed and evaluated in accordance with the relevant measures of reproducibility. For each of the secondary outcomes, the ability of PCS, HADS, HPDT, Max-VAS and VAS-AUC (following LTS), to predict individual variations in areas of secondary hyperalgesia will be investigated by linear regression. Significance of the predictors will be assessed by Analysis of variance (ANOVA) methods and their predictive abilities will be quantified by various summaries of prediction errors including 95% prediction intervals for the predictions

For all analyses, an intention-to-test analysis will be performed including all subjects who participated in the first experimental day. Analyses will be based on all observed data. If missingness exceeds 5% and there is indication of violation of “missing completely at random” (MCAR) a sensitivity analysis based on an appropriate model for missingness at random (MAR) or not at random (MNAR) will be performed.

A family wise error rate of 0.05 will be used and simultaneous assessment of multiple p-values will be subjected to single-step adjustment

#

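### With one mapping per participant per day, intra-observer variance cannot be separated from between-day change, and the inter-observer limits of agreement include day-to-day variation

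*Protocol*

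**What the plan says.** The Primary outcome section sets the aim: "To determine the intra- and inter-individual variance, and the inter- and intra-observer variance of the secondary hyperalgesia areas", measured "on 4 separate experimental days with two different observers". Intra-observer variance thus stands beside intra-individual variance as a quantity of its own. The protocol does not define either term.

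The measurement scheme is spread over several sections:

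- General procedure: "There will be 2 different investigators responsible for the testing", and their order is randomised "so the same investigator will not be responsible for 2 consecutive experimental days".
- General procedure: testing takes place in a room "where only the study participant and the investigator will be present".
- General procedure, study-day timetable: "0 min: Brief thermal sensitisation" is the only sensitisation of the day. HPDT and LTS follow at 7 and 10 minutes.
- Assessment of secondary hyperalgesia: four paths are stimulated and "the transverse and longitudinal axes will be measured for later area calculation". No repeat mapping is described.
- Case Report Forms: one calculated area is listed among the results for study days 1 to 4.

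The Plan of statistical analysis has a variance component model with three sources (participant, day, observer) and a limits-of-agreement "plot for agreement between areas of secondary hyperalgesia on different experimental days and different observers".

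**The concern.** Two things are at stake.

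First, a reader of the primary outcome expects two distinct answers: how much a person's area truly changes between days, and how repeatable an observer is. The study is meant to show low intra-individual variability and to inform the sample size of later studies. Both uses depend on where the within-person spread comes from: repeat mapping would reduce measurement error but not biological change. If one number is reported under two names, it will look as though that question has been answered.

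Second, wide inter-observer limits would naturally be read as poor agreement between observers. Here they may reflect nothing more than the participant being tested on a different day.

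**Working it through.** The protocol gives no variance, no width for the limits and no target precision, so there is no figure of its own to reproduce. Two checks apply.

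**1. What the design can separate**

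With two observers and no observer on consecutive days, the only sequences are ABAB and BABA. Let P be participant variance, PO participant-by-observer variance, PD a participant's true day-to-day variance, and E the observer's own mapping error. For two areas from one participant:

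- P contributes to every pair.
- PO contributes only when the observer is the same.
- PD contributes only when the day is the same.
- E contributes only when the mapping is the same.

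With one mapping per day, same day and same mapping are the same condition, so PD and E have identical covariance matrices. The four matrices have rank 3 of 4: P, PO and the sum PD + E are estimable, and PD and E individually are not. With a second mapping in the same session, by the same observer or the other one, the rank becomes 4 of 4.

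A simulation agrees (50 participants, 4,000 runs, P = 1, PD + E = 0.25, no observer difference). The share of E is not in the protocol, so it was varied:

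| E as share of PD + E | Same-observer variance recovered | Inter-observer half-width, single-day pairs | Half-width within one session, 1.96·√(2E) |
|---|---|---|---|
| 10% | 0.250 | 1.379 | 0.44 |
| 50% | 0.250 | 1.379 | 0.98 |
| 90% | 0.250 | 1.381 | 1.31 |

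Half-widths are in between-participant SD. The planned data look the same in all three cases, while true same-session agreement differs threefold.

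**2. What the inter-observer limits contain**

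Any A-minus-B difference spans two days. For single-day pairs its variance is 2(PO + PD + E). A mean observer difference shifts the centre of the limits, not their width.

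The Sample size estimation section says only that the intra/inter ratio could be above 25%, so 25% is an assumption here. With P = 1 and PD + E = 0.25 the total is 1.25 and the within-person share is 0.25/1.25 = 0.20. With PO = 0:

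- Single-day pairs: 1.96·√(2 × 0.20) = ±1.24 total SD. In between-participant SD this is 1.96·√0.5 = ±1.39, against about 1.38 simulated.
- Each observer's two days averaged: 1.96·√0.20 = ±0.88 total SD.

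At other assumed ratios r the within-person share is r/(1 + r):

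| Ratio | Share | Single-day pairs | Averaged |
|---|---|---|---|
| 25% | 0.20 | ±1.24 | ±0.88 |
| 50% | 0.333 | ±1.60 | ±1.13 |
| 100% | 0.50 | ±1.96 | ±1.39 |

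Real disagreement adds little to the width. With PO = 0.05 at the 25% ratio, the half-width is 1.96·√(2 × 0.30) = 1.52 between-participant SD, against 1.39 without it.

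**3. A limit on comparing the two sets of limits**

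Same-observer pairs (days 1–3 and 2–4) are always two study days apart. Different-observer pairs are one apart (1–2, 2–3, 3–4) or three apart (1–4). If day effects within a person are serially correlated, say with an assumed correlation of 0.5 that decays by power of lag, PD enters the difference with these factors:

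- same observer: 1 − 0.5² = 0.75;
- different observer: (3 × 0.5 + 0.875)/4 = 0.59.

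The different-observer limits could then be the narrower ones even when observers truly disagree.

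**The case against.** The strongest reply is about definition. Intra-observer variance is undefined, and the outcome is expressly set over four days, so it can be read as same-observer, between-day variance. Each observer tests each participant on two days, so that quantity is estimable. It also differs from total intra-individual variance over four days, which includes the observer terms. The planned model names only three sources and never claims to fit a fourth.

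This stands, and it rules out the tempting inference that part of the primary outcome yields no estimate at all. But on that reading the quantity is PD + E, which is the within-person residual under a second name, so the wording still needs to change.

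Second, the analysis text already mentions different days alongside different observers, the model gives readers more than the plot, and the choice and labelling of pairs may sit in an SAP not shown here. That is fair as to labelling. No analysis, however, can form a same-day observer pair from these data.

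Third, the ±1.24 is not the protocol's figure. It depends on an assumed ratio and on single-day pairs, and averaging gives ±0.88. That is correct, and the number serves only as an illustration.

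**Conclusion.** The point holds in a limited form. Observer repeatability and true between-day change are estimable only as a sum, and the inter-observer limits include between-day variation whatever the observers do. Both follow from the measurement scheme and need no numerical assumption. The sizes do need one: ±1.24 total SD (±0.88 with averaging) assumes a 25% ratio, no participant-by-observer variance and no serial correlation.

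A reader might infer that observer agreement cannot be assessed at all. The documents do not support this: both observers see every participant twice, so the mean observer difference and participant-by-observer variance are estimable. Nor is the study's main aim, low intra-individual against high inter-individual variability, affected. This should be fixed, but the primary outcome is not invalid.

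**What to change.** In the Primary outcome section, restate the quantities as:

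- (a) inter-individual variance;
- (b) one combined same-observer, between-day variance, described as biological plus measurement;
- (c) the mean observer difference and the participant-by-observer variance.

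Make no claim of a separate intra-observer variance.

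In the Plan of statistical analysis:

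- Label the inter-observer limits as different-observer, different-day limits and present them beside the same-observer, different-day limits.
- Base the conclusion on observer agreement on the model's observer terms, with day included as an effect, and not on the width of the inter-observer plot alone.
- State that this contrast assumes no strong serial correlation between days, because same-observer pairs are two study days apart and different-observer pairs one or three.

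The cost is rewording: no added visits, mappings or staff. The downside is that one separately named quantity is withdrawn. Keeping it would require a second mapping within at least some sessions, which the present scheme does not include.

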**Secondary outcomes**

To evaluate how precise the scores of PCS and HADS, total and sub-scores, predict the size of the area of secondary hyperalgesia following brief thermal sensitization.

To evaluate how precise HPDT and pain during 1 min. thermal stimulation of the skin (LTS) predict the size of the area of secondary hyperalgesia following brief thermal sensitization.

The results from this study are to be used in evaluating sample size in future studies.

# **Ethics**

## **Considerations in connection with the study as a whole**

By applying experimental pain models on healthy volunteers it is possible to study basic pain mechanisms under standardised conditions. Results from such studies may be used to optimise or change current clinical analgesic therapies, which may benefit a large population of patients.

Our overall aim with this study is that we in the future, by simple tests will be able to phenotype patients and estimate their risk of developing pain, thus estimating their pain disposition. An individualised approach to pain and analgesic treatment may be a way to reduce the incidence of acute and chronic pain, by individualising the analgesic regime.

A reduction of the incidence of acute and chronic pain will be of substantial significance to the individual patient. This will in addition also have a great socioeconomic importance, given that a large proportion of the patients with chronic pain are fully or partly excluded from active work.
The study will be conducted in accordance with the principles of the Declaration of Helsinki. The protocol will be submitted to the local Research Ethics Committees and the Danish Data Protection Agency for approval. The investigator will also inform the Research Ethics Committee and the Danish Data Protection Agency of any significant or major changes in the protocol. The study will be registered in the international database clinicaltrials.gov.

## **Risks, adverse effects, disadvantages, etc.**

Brief Thermal Sensitisation with computer-controlled thermode does not cause skin damage. In rare cases, changes comparable with a first degree sun burn may appear.

Long thermal Stimulation and evaluation of Heat Pain Detection Thresholds do not cause skin damage, and is not associated with any known adverse effects. It is our assessment that adverse effects and risks in this study are very low, hence, participation in this study is considered to be of very low risk.

Participation in the study is not expected to result in further harm, tests or examinations than described above.

## **Information about and consent from patients**

The study participants will be recruited by advertisement in the student magazine “Medicinske studenter Organisationers Kommunikationsorgan” (MOK), at the Faculty of Health, Copenhagen University, and on the website: [www.forsøgspersoner.dk](http://www.forsøgspersoner.dk).

The volunteers that sign up for the study will receive a copy of the written study information for participants, and the participant is verbally informed about the possibility of having a companion present to the following interview. At the interview the volunteer is verbally informed about the study in an easy comprehensible form. The verbal information will be given by one of the investigators. The interview will be conducted in a closed room without distractions or interruptions. The volunteer will be given time to consider the request.

All volunteers taking part in the study must provide their oral and written informed consent before they are included in the study. It is the investigator's duty to inform the participants so that they are fully aware of all aspects of the study.

Participants may at any time withdraw their consent to participate in the study. If the participant decides to do this, this will not impair the participant’s relationship with the investigator and the investigator will not question the decision of the participant.

